**Methods:**

One hundred and fifty mothers (50 Anglo-Australian, 50 Italian-Australian, 50 Vietnamese-Australian) will be recruited, with four or more other family members across three generations, including a child (aged 10–18 years). Each family is randomly assigned to intervention or control. At baseline and 6-month follow-up, all participants complete surveys to assess dietary and physical activity intentions and behaviors, attitudes towards food, and perceived disease risk. Intervention families receive a visual pedigree detailing their FHH of diabetes, heart disease, breast and bowel cancer, a health education workbook to ascertain members’ disease risk (i.e. average or above average risk), and screening and primary prevention recommendations. After completion of follow-up assessments, controls will receive their pedigree and workbook. The primary hypothesis is that attitudes and lifestyle behaviors will improve more within families exposed to FHH feedback, although the extent of this improvement may vary between families from different ethnic backgrounds. Additionally, the extent of improvement in the treatment group will be moderated by the level of family disease risk, with above-average risk leading to greater improvement. A secondary aim will explore different family members’ roles in message distribution and collective responses to risk using social network approaches and to compare network functioning between families with different ethnic backgrounds.

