#### Baseline survey

At baseline, all participants (i.e., all family members nested in the 150 families) will complete a survey to assess lifestyle behaviors, including diet and physical activity, attitudes towards food and perceived disease risk. This survey will be available in either a paper or online format and takes no longer than 45 min to complete. There are two baseline forms of the questionnaire, one for adults and one for children. The adult version is identical across ethnic groups, with the exception of an acculturation questionnaire which appears in the Italian and Vietnamese versions. As part of their baseline survey all index mothers and fathers will be invited to complete a FHH, which involves indicating disease history for heart disease, diabetes, breast and colorectal cancer for the mothers’ and fathers’ first and second degree relatives. Measures included in the parent and child versions of the baseline are described in Table 1.

**Table 1 Tab1:** Summary of measures included and point of data collection

Families, food and eating survey	Baseline	Endpoint	Adult	Child
Section 1: Cultural identity and background (7 items)				
Country of origin and parents’ origin, language spoken at home.	X		X	X
Section 2: Lifestyle (current behavior determined from previous week)^1^ (13 items)				
Smoking status	X	X	X	
Vigorous Physical Activity:				
• Days per week	X	X	X	X
• Hours/Minutes per day	X	X	X	X
Moderate Physical Activity:				
• Days per week	X	X	X	X
• Hours/Minutes per day	X	X	X	X
Sedentary Behavior:				
• Hours/Minutes per day on a weekday	X	X	X	X
• Hours/Minutes per day on the weekend	X	X	X	X
• Sedentary activities (Children only) – hours per day on a weekday	X	X		X
• Sedentary activities (Children only) – hours per day on a weekend	X	X		X
Family physical activity				
• Days per week	X	X	X	X
• Hours/Minutes per day	X	X	X	X
Serves of fruit per day averaged over previous week	X	X	X	X
Serves of vegetables per day averaged over previous week	X	X	X	X
Number of visits to franchised fast food restaurants in the previous week	X	X	X	X
Serves of high fat and/or high sugar “snacks” per day averaged over previous week	X	X	X	X
Alcohol consumption				
• Days on which alcohol consumed in past week	X	X	X	
• Average number of standard drinks on drinking days	X	X	X	
Section 3: Intended Lifestyle Changes (Minimum 1 item, Maximum 6 items)^2^				
Considering Lifestyle change (yes or no)	X	X	X	X
Areas: Fruit and Vegetable consumption; Physical Activity;	X	X	X	X

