#### Family health history intervention

Three months after an intervention family has provided the last baseline survey they will receive a health education booklet, entitled ‘Families SHARE’. This will contain a visual family pedigree of the previously identified first and second degree relatives of the index parents with disease markers highlighted for heart disease, diabetes, breast and colorectal cancer. The ‘Families SHARE’ booklet contains a clear description of a family pedigree with guidance to help participants interpret their own and other family members’ risk for disease using the pedigree. In addition, the booklet contains information about genetic and environmental risk for disease along with behavioral and screening recommendations.

The control group of families will receive nothing between baseline and follow-up, and will receive their ‘Families SHARE’ booklet containing their family’s health history upon completion of the study.

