### Outcome measures

The primary outcome tested will be the changes in intentions to improve food choices following exposure the FHH the main hypothesis is that exposure to the FHH will improve intended dietary behaviour with the extent of improvement dependent about the nature of risk within the family (i.e., above average v average). Secondary analyses will focus on exploration of the communication, social influence, and support networks within families at baseline, and how these differ between cultural groups and are related to health behaviors. Changes in the patterns or ‘structure’ of these social networks after exposure to the Families SHARE intervention will be compared to changes in the control families. For example, we will test if exposure to Families SHARE activates a communal coping response, evidenced by an increase in density of communication ties and encouragement ties among family members, and if this moderates health behaviour outcomes.

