### Statistical analyses

#### Primary outcomes

The primary outcome is change on the diet-related intentions of each individual in the study, according to group assignment (Treatment (FHH) versus Control), controlling for ethnic background (Anglo, Italian, and Vietnamese). The primary outcomes are; intentions to change diet, specifically, fruit and vegetable and fibre consumption. Secondary outcomes include intentions to change physical activity, alcohol consumption and smoking. These initial analyses will consider differential effectiveness of the intervention according to extent of family risk for chronic disease and the ethnic background of the families.

While the time period between assessments is short, which will limit potential behavioural changes over the 6-month period, levels of consumption and participation in ancillary health-linked lifestyle choices will also be assessed and compared between groups and over time. In addition, we will establish the extent to which change is moderated within the intervention group by the nature of the feedback (average v above average risk) and the potential moderating or mediating effects of cultural and social capital, health locus of control, optimism in the full sample, and acculturation within the minority groups.

A multilevel modelling approach, which accounts for participants being nested in families, will be used to look at the effect of the intervention, and ethnicity, on intentions to change behaviors post intervention. We hypothesize a main effect for the intervention condition so that intentions and behavior become more consistent with feedback recommendations following exposure to the FHH assessment than does that of the control group. Comparison between ethnic groups will test for efficacy differences.

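### The plan sets a within-arm analysis of risk moderation beside an unspecified between-arm one; the within-arm contrast is confounded, and an arm-by-risk interaction should decide the risk hypothesis

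*Protocol article*

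**What the plan says.** The protocol article addresses moderation by family risk in four places, and they do not describe the same analysis.

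- **Abstract, Methods.** The directional hypothesis is framed inside one arm: "the extent of improvement in the treatment group will be moderated by the level of family disease risk", with above-average risk expected to bring the greater improvement.
- **Outcome measures.** Risk dependence is part of the main hypothesis, with no restriction to one arm: "with the extent of improvement dependent about the nature of risk within the family".
- **Statistical analyses, Primary outcomes, first paragraph.** The primary outcome is compared "according to group assignment (Treatment (FHH) versus Control), controlling for ethnic background". The paragraph ends: "These initial analyses will consider differential effectiveness of the intervention according to extent of family risk for chronic disease", and adds ethnic background.
- **Same section, second paragraph.** As an addition, the team will establish "the extent to which change is moderated within the intervention group by the nature of the feedback". The same sentence assigns locus of control, optimism and social capital to the full sample and acculturation to the minority groups, so limiting risk to the intervention arm looks deliberate.

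The model under Sample size has intervention, baseline intentions and ethnic group. The multilevel model under Primary outcomes names intervention and ethnicity. Neither names risk.

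The information needed to classify control families is collected. Under Baseline survey, "all index mothers and fathers will be invited to complete a FHH". Under Family health history intervention, controls "will receive their ‘Families SHARE’ booklet containing their family’s health history upon completion of the study".

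**The concern.** Families are randomised to the workbook, not to a risk level. Above-average-risk families may start with different intentions, may already include ill relatives, and may regress to the mean differently. Any of these could make their six-month change differ from that of average-risk families with no workbook at all. Comparing the two kinds of family inside the intervention arm is therefore an observational comparison of change.

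At stake is one of the trial's headline claims, that an above-average risk message motivates more improvement. The control arm shows how change differs by risk without the workbook, but the within-arm contrast makes no use of it. As two analyses of the same question are mentioned and neither is given priority, the confounded one could end up carrying the claim.

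**Working it through.** **1. The plan's own figure.** Sample size gives f = 0.25, type I error 0.05, power 0.80 and 132 families, for the intervention effect. With two equal arms f = 0.25 is a standardised difference of 0.5. A family-level F test with 1 numerator df and noncentrality N × f² = N × 0.0625 first reaches 0.80 at N = 128 (power 0.801). Rounding 128 up to six equal arm-by-ethnicity cells gives 6 × 22 = 132, where power is 0.813. The stated figure is reproduced. It covers the main effect only; nothing in it sizes a risk interaction.

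**2. Inputs for the risk contrast.**
- Families per arm: 132 / 2 = 66 (from the Sample size section).
- Risk split within an arm: 33/33 or 50/16 (assumed; the documents give none).
- Natural difference in change between risk groups, the same in both arms: 0, 0.3 or 0.5 SD of the family-level outcome (assumed; the documents give none).
- True moderation by the workbook: none.
- Two-sided 5% tests (sidedness assumed).

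**3. Within-arm contrast.** SE = √(1/n₁ + 1/n₂) in SD units, 64 df, noncentrality = natural difference / SE, noncentral t.

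| Split | SE | Natural difference | Noncentrality | False-positive rate |
|---|---|---|---|---|
| 33/33 | 0.246 | 0.3 | 1.22 | 0.225 |
| 33/33 | 0.246 | 0.5 | 2.03 | 0.516 |
| 50/16 | 0.287 | 0.3 | 1.04 | 0.177 |
| 50/16 | 0.287 | 0.5 | 1.74 | 0.403 |
| either | – | 0 | 0 | 0.05 |

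**4. Arm-by-risk interaction.** The natural difference appears in both arms and cancels, so the test keeps its 5% level whatever that difference is. A simulation (20,000 replicates, 66 families per arm, 30% or 50% above average) agrees. At 0.3 SD the within-arm test rejected in 19-22% of trials and at 0.5 SD in 46-51%, while the interaction stayed at about 5%. With no natural difference both were at about 5%.

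**5. What the interaction costs.** SE = √(2 × (1/n₁ + 1/n₂)). For 33/33 in each arm this is √(4/33) = 0.348; for 50/16 it is 0.406. The difference detectable at 80% power is (1.96 + 0.84) × SE, that is 0.98 SD and 1.14 SD. In the simulation, power was about 26-30% for a true interaction of 0.5 SD and 75-81% for 1.0 SD. The SE is √2 = 1.41 times that of the within-arm contrast.

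**The case against.** A reader might infer that risk moderation is tested only inside the intervention arm and that the claim would have no valid control. The documents do not support this. The first paragraph of Primary outcomes defines a treatment-versus-control analysis and says it will consider differential effectiveness by family risk. Read naturally, that is a between-arm comparison. The within-arm analysis is introduced afterwards as an addition.

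Three further points can fairly be made.

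- **The exact model term can be left to a fuller document.** True, and its absence alone would be no finding. The point here is a stated choice: one arm is named for the risk analysis, and the Abstract repeats that framing. The between-arm sentence does not say which analysis decides the hypothesis.
- **Baseline intentions are a covariate in the Sample size model.** If the moderation analysis uses that model, differences in starting intention and regression to the mean are reduced. This weakens two of the three mechanisms. It does not remove differences in existing illness or other correlates of family risk.
- **The size of the bias is assumed.** Also true. Nothing in the documents shows that change differs by risk without the workbook, and if it does not, the within-arm test holds its 5% level. The bias is possible, not certain.

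It is also fair that moderation hypotheses need not be powered, and that Primary outcomes already hypothesises a main effect. But Outcome measures writes risk dependence into the main hypothesis, so its rank is not consistent across sections.

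**Conclusion.** The point holds in a limited form. The plan mentions a between-arm look at family risk, but it also fixes a within-arm analysis that matches the Abstract's directional hypothesis, names no risk term in its models, and does not say which analysis decides. The within-arm contrast is not protected by randomisation.

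If change differs by risk without the workbook by 0.3 SD, the within-arm test would wrongly indicate moderation in about 18-22% of trials; at 0.5 SD, in about 40-52%. These rates rest on 66 families in the arm, the assumed splits, no true moderation and no reduction from baseline adjustment. The interaction holds 5% under the same conditions but is imprecise, so it supports an estimate better than a pass/fail test.

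**What to change.** 1. Have the study team classify every family in both arms as average or above average from the baseline family health history, using the workbook algorithm, blind to arm and outcome.
2. State that the risk hypothesis is judged by the arm-by-risk interaction in the multilevel model adjusted for baseline intentions, reported as an estimate with a 95% CI.
3. Keep any contrast within the intervention arm if wanted, labelled descriptive.
4. Align the Abstract, Outcome measures and Primary outcomes so that the intervention main effect, for which the 132 families were sized, is the primary hypothesis and risk moderation is secondary.

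The work is scoring control families whose histories are collected at baseline and whose booklets are prepared in any case, plus changes of wording. The price is precision: an interval about 1.41 times as wide as the within-arm one, with only about 1.0-1.1 SD detectable at 80% power.

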#### Secondary outcomes

Building on the study of Feunekes et al. [6], we will first explore the extent to which diet and eating behaviors correlate amongst different types of family ties at baseline (e.g., parent-child, spouse, etc). Social network analyses will then be undertaken to summarize the characteristics of family social networks at baseline and follow up, which will allow us to test if there is differential change in the structure of these networks across study conditions, and across ethnic groups. For example, we expect the density of communication ties (i.e., proportion of actual relative to possible ties) and density of encouragement ties among family members receiving the intervention to increase, driven by a communal coping response. Relational structures such as *mutual* influence and encouragement will also be analysed, to understand their role in promoting change in the main dietary outcome measures, and to determine if these processes differ across intervention and control conditions, and across ethnic groups. Social network analysis will also be used to describe the roles of various family members in these health communication and support networks, to identify family members playing important roles in initiating or maintaining the targeted health behaviors across three generations, and family members who play key roles in facilitating or hindering behaviour change.

### Time plan

Participant recruitment will be ‘rolling’, as families enter the study they will commence baseline and their own 6-month time-frame.

## Discussion

To examine intergenerational transmission of health-related behaviors in families with different ethnic backgrounds, and to assess the impact of FHH-based risk assessment across generations in an appropriately controlled way, it is necessary to apply very strict inclusion criteria. These include the need to have members from at least three generations available to participate; enrolling participants who are prepared to provide information about their family’s health history; potentially collecting data from “blended families” and requiring at least a moderate level of English language skill from most participants.

Enrolling families using these criteria is likely to require significant time. Moreover, the proposal to identify families through the mother may create further difficulties, particularly where English language is poor and the mother is at home. There is little guidance available in the research literature on best practice for recruitment of complex sampling frames that involves people from multiple ethnic backgrounds and age groups. We will therefore use the experience garnered in the proposed study to provide a case study report of the problems encountered and any variations required to the approaches described earlier.

The possibility of attrition associated with the longitudinal design and complex requirements will need to be closely managed. We hope to minimise this by the design and distribution of a regular newsletter highlighting progress in the study and the importance of participation and including items that might be of interest to the families (e.g., recipes and local events) [50].

The issues of research translation and generalizability will not be adequately addressed within the context of the current study design. Our focus is on efficacy rather than effectiveness and managing threats to internal rather than external validity. Assuming efficacy can be established; further work will be required to address the process by which exposure to family history of disease might best be achieved. Additionally, the receptivity of other groups in the community to this information cannot be assumed. Anglo, Italian and Vietnamese Australians were selected for the current study because they are among the larger groups in South Australia, improving the probability of recruiting the required numbers [51]. Moreover, the two non-English speaking groups represent different waves of migration to Australia [52], different incidences of overweight and different traditional eating habits [40, 41]. If the intervention is found to be efficacious in motivating intentions to change lifestyle behaviors in families, it will be necessary to evaluate its use and effectiveness in the wider population, across groups with different ethnic and other background characteristics.

## Abbreviation

FHH: Family health history
